#### Recruitment to the effect evaluation and economic evaluation

Potential participants are recruited in two ways. 1) The Norwegian Labour and Welfare Service (NAV) will provide monthly lists of persons meeting the inclusion criteria. An assigned project co-worker sends out invitations to potential participants who accept to participate by contacting the research group. Persons who accept to participate are invited to an out-patient screening clinic for clinical examination and interview before inclusion. 2) General practitioners (GPs) refer patients to the study and the rehabilitation program. The GPs will be provided with information of the project through written leaflets, the website of the rehabilitation centre (www.stolav.no/hysneshelsefort), and can call a project co-worker for any questions. The GPs will refer potential participants directly to the out-patient screening clinic for clinical examination and interview. Besides the project co-worker who sends out the invitation letters, none of the researchers in the project will know the identity of potential participant, until the person accepts to participate through answering the invitation letter or accepts to being referred to the program by their GP.

All participants will complete baseline study outcome measurements and several screening questionnaires before an out-patient screening is performed. The screening is conducted by a medical doctor, a psychologist and physiotherapist during clinical examination and interview. The clinic assesses the final eligibility before randomization and excludes all persons who do not fit the inclusion criteria. The personnel at the screening clinic will also give oral and written information about the study, and emphasize that agreeing to participate includes being randomized to a program with or without a workplace intervention. All participants who are included by the screening clinic will sign a written consent form prior to randomization. Taking part in the RCT will be a prerequisite for participation in the rehabilitation program and the intervention. The participants can decline participation and withdraw from the study (and program) at any point.

#### Randomization

Persons who are found eligible and sign an informed consent will be randomized to the intervention arm (rehabilitation program with a workplace intervention) or the control arm (rehabilitation program only). Block randomization with unknown block sizes is performed using a web-based program delivered by a third party - the Unit for Applied Clinical Research at the Norwegian University of Science and Technology.

#### Recruitment to qualitative and mixed methods studies

All participants in the RCT will be eligible to take part in qualitative studies. Participants will be recruited strategically to inform the specific research aims. Potential participants will be given written and oral information about the studies and all participants will sign a consent form before taking part in interviews or observation. Potential participants in the first of the two qualitative studies are all rehabilitation therapists at the center, including all those providing the workplace intervention. They will be contacted directly by the researchers, and we aim to recruit 10–15 therapists. For the observation in the second qualitative study, all participants in one program group will receive written information and asked to consent to having a researcher present in their group during the rehabilitation program. All participants in the group must consent to the observation. Potential participants in the second qualitative study are the participants in the intervention arm, their employers and rehabilitation therapists. First, the participant will be given written information, and asked to take part in interviews and whether a researcher can observe the workplace intervention. If the participant consents, their employer will be contacted with the same information. The rehabilitation therapist will also be asked by the researcher to take part in interviews. We aim to recruit a sample where the participants’ gender, type of occupation, age, and length of sickness absence is varied. We aim to recruit 10–15 triads (participant, therapist and employer). Potential participants in the mixed methods study are the participants (from intervention group and control group) who have completed questionnaires 4 months after the end of the rehabilitation program. A sample of approximately 20 of these participants will be asked to take part in individual interviews. This will be a strategic sample to explore their perspectives on the return to work process in interviews four months after the rehabilitation programs, and to elaborate on quantitative data already collected in the RCT on the same subject.

### The occupational rehabilitation program

Regardless of group allocation in the RCT, all study participants take part in an occupational rehabilitation program. The program is composed of elements that are assumed to be useful in occupational rehabilitation for long-term sickness, and includes physical exercise, psychological therapy, and work related problem solving. Hysnes Rehabilitation Center (www.stolav.no/hysneshelsefort) is the setting for the occupational rehabilitation programs. The center was established as part of St. Olav’s Hospital and is located in the municipality of Rissa, a 50 min boat ride or 90 min drive from Trondheim, the third largest city (181.500 inhabitants) in Norway. The center has provided in-patient occupational rehabilitation programs since 2010.

The rehabilitation program lasts four weeks; the first two weeks at the rehabilitation center, the third week at home, and the fourth week at the center, engaging participants in full ‘work’ days, aiming to establish normal daily routines. The program is provided by interdisciplinary teams consisting of psychologists, physiotherapists, exercise physiologists, nurses, physician and welfare case worker provide the programs. All professionals are trained as ACT therapists. Each therapist treats 2–4 clients individually and in groups, focusing on behavior change and coping. Two therapists are assigned to each group which includes 6–8 participants. A mid-way report and a final report are sent to the GP. If the participant agrees, the reports are also sent to the participant’s welfare office and employer.

#### Physical exercise

Physical exercise is utilized to improve health, fitness, functional capacities, and to reduce fear-avoidance related to physical activity. An exercise plan is made for each participant and follow-up is provided during the program, both in groups and individually. The main objective for individual follow-up of exercise during the program is to ensure that the exercise plan is suitable and realistic and can be useful for the participant after the program.

#### Acceptance and commitment therapy (ACT)

The psychological therapy approach is ACT, an approach which uses acceptance and mindfulness strategies, along with commitment and behaviour change strategies, to increase psychological flexibility [42, 43]. ACT aims to improve work functioning, general skills of psychological flexibility and motivation to return to work despite the presence of pain or other symptoms [43]. Psychological flexibility is described as “the ability to contact the present moment more fully as a conscious human being, and to change or persist in behaviour when doing so serves valued ends” [42, 43]. ACT is increasingly used in various settings and for different patient groups [46] and has shown positive results in several areas [47–51]. A written manual for the ACT sessions (both in groups and individually) has been made by health professionals at the rehabilitation centre in collaboration with an experienced psychologist. The manual describes the intended aims and therapeutic processes of each session, including content and techniques. For every session, it also gives examples of observable participant behaviour that could indicate an increase in psychological flexibility. To develop and strengthen the rehabilitations therapists’ use of the ACT approach, they receive continuous individual supervision from an experienced psychologist. In addition, visual recordings and observation of therapy sessions are used in individual and group supervision of the therapists, to strengthen fidelity to the approach.

#### Work-related problem solving

Work-related problem solving aims to identify challenges and possibilities regarding the return to work process, in order to create an individual return to work plan. Interaction with relevant stakeholders (such as employer, colleagues, GP, welfare case worker or family members), will be discussed, as well as commenced during the rehabilitation process if the participant finds it suitable and helpful. The participant thus chooses whether and how to involve any of these stakeholders. All participants will, in collaboration with their rehabilitation therapist, create their own return to work-plan with individually tailored elements. Here, relevant challenges, measures and solutions regarding the workplace and other parts of the participant’s life will be described (for example work adjustments, as well as goals for physical exercise and social life). The employer contributes to the part of the plan which concerns issues at the workplace, and receives this part of the final plan. If the participant consents, the employer receives the whole plan. In addition, the program includes educational sessions on sleep, pain, nutrition and work-related aspects. ACT is the common ground for and fuels every aspect of the program; an emphasis on developing generalizable and lasting behaviour change that the participants consciously choose in accordance with personal values.

### The workplace intervention

The workplace intervention is inspired by previous successful workplace interventions [7, 16, 52, 53], and was developed by professionals at the rehabilitation center and the research group, with input from the Norwegian labor and welfare administration. The intervention is adapted to the time frame of this rehabilitation program, as well as the geographical, sociocultural and socioeconomic context, also taking into account that these programs will be delivered within a specialist hospital system.

The workplace intervention will consist of a preparatory part during the first two weeks, a meeting at the workplace in the third week of the program, and follow-up work related to the meeting in week four. The individual therapy sessions during week 1 and 2 are used to map the participant’s work situation, as well as any potential challenges and possibilities in the return to work process. During the first two weeks of the rehabilitation program the employer is contacted and an appointment for the workplace meeting is made. A one-hour work-specific ACT group session is held during week 2. This session focuses on the participants’ perceptions related to the return to work process, and the possibilities of coping at work despite disabilities are explored.

The participant and the rehabilitation therapists will meet 15–30 min before the workplace meeting. If it is not agreed upon earlier, they will discuss any limitations of topics which will be discussed with the employer present. A tour on the workplace to view the work arrangements is conducted when found relevant by the participant and rehabilitation therapist. The meeting lasts approximately two hours, and includes the participant, his or her employer, and the participant’s rehabilitation therapist. From the employer, the participant’s closest leader should always attend, but other persons, such as employee representative or personnel safety representative, considered to be helpful for the return to work process (e.g. due to necessary decision making authority) could also take part. The participant’s GP and/or labor and welfare case worker will be informed about the meeting and will be involved when appropriate. The rehabilitation therapist chairs the meeting. The objective is to discuss and plan the participant’s return to work process and the actual return. This encompasses identifying the participant and employer’s views on any challenges in returning to work, and to discuss potential measures. Conclusions will be made and the responsibility for implementation of any measures will be established.

After the workplace meeting the rehabilitation therapist will contact the employer to ensure that actions agreed upon in the meeting are taken and that measures and solutions will be implemented. A report is sent to those who took part. The participant and the rehabilitation therapist subsequently will discuss the experiences and outcomes from the workplace meeting. The return to work plan is concluded and mailed to the participant’s general practitioner. The plan is mailed to the employer if the participant finds it helpful.

### Study design

The study includes three main parts; an effect evaluation, an economical evaluation, and two qualitative studies and one mixed methods study.

#### Effect and economic evaluation

The effect evaluation is conducted as a randomized controlled study with a parallel group design. There are three main research questions in the effect evaluation:Is an in-patient rehabilitation program with a workplace intervention more effective in increasing return to work (time until full sustainable return to work) and reducing sickness absence (total number of sickness absence days during 12 months of follow-up from inclusion), compared to the rehabilitation program only?Is an in-patient rehabilitation program with a workplace intervention more effective in improving health, quality of life, and readiness for return to work, compared with the rehabilitation program only?Is the in-patient rehabilitation program with a workplace intervention cost- effective, compared to the rehabilitation program only?

#### Qualitative and mixed methods studies

Three different studies will be conducted:A qualitative interview study will investigate how the rehabilitation therapists attend to the program’s main objective – return to work – within a rehabilitation program based on the ACT approach. This study will explore the rehabilitation therapists’ experiences with using a novel therapy approach to enhance return to work. (Study A)A qualitative interview and observation study will investigate the different stakeholders´ (sick-listed person, employer, and rehabilitation therapist’s) experiences of the feasibility and outcomes from a workplace intervention. (Study B)And a mixed methods study, including quantitative data from questionnaires and qualitative data from interviews, will investigate and elaborate on any changes in the participants’ expectations to return to work 4 months after a rehabilitation program with or without a workplace intervention. (Study C)

### Data collection

#### Effect evaluation

Data on sickness benefits and other social benefits will be based on register data from the National Welfare Administration. Self-reported data will be collected by internet based questionnaires (www.checkware.com) before screening, before the rehabilitation program starts, right after the rehabilitation program has ended, and 4, 8 and 12 months after the end of the rehabilitation program. Participants are invited by text messages to access the website and answer the questionnaires.

*Primary outcomes*
Time from inclusion (i.e. after outpatient screening) until full sustainable return to work (i.e. for at least four weeks without relapse), obtained by national registers.Total number of sickness absence days during 12 months of follow-up from inclusion, obtained by national registers.

*Secondary outcomes*
Readiness, beliefs and motivation for return to work (RRTW) [54].Expectations regarding future work participation and sick leave:

*How long do you think you will be on sick leave from today?* (Less than 2 months; 3–6 months; 7–12 months; more than 12 months; I am currently not on sick leave).

*Given your current health situation, do you think you will be receiving full sick-leave benefits six months from now?* (Yes; no).

*Given your current health situation, do you think you will be receiving graded sick leave benefits six months from now?* (Yes, less than 50%; yes, 50% or more).

(The questions were developed during workshops with the research group.)Work adjustments and consideration from employer and colleagues:

*Has your employer adjusted your work situation according to your health complaints (*e.g. *changes in work tasks, working hours or facilities)?* (Yes; no; I do not need adjustments).

*To which extent do you feel that your*
*employer*
*show consideration for your level of functioning?* (Very much; to some extent; not much; I do not need special consideration).

*To which extent do you feel that your*
*colleagues*
*show consideration for your level of functioning?* (Very much; to some extent; not much; I do not need special consideration)Job satisfaction:

*How do you like your work?* (Not at all; not so much; good; very much).Return to work self-efficacy (RTWSE-19) [55].Health-related quality of life by 15D (15 dimensions) [56].Perceived general health:

*How is your health now?* (Poor; not so good; good; very good.)Pain intensity and pain sites by a body pain chart and question 3–5 from the Brief Pain Inventory (BPI) [57].Physical activity levels measured by three items concerning frequency, intensity and duration of exercise from the third wave of the HUNT study (The HUNT study, Norway. [https://hunt-db.medisin.ntnu.no/hunt-db/#/instrument/130]).Fear-avoidance beliefs about work and physical activity [58].Psychological flexibility and acceptance [59].Psychological flexibility and acceptance related to work [60].Perceived work ability:

*How would you rate your current work ability compared with the lifetime best?*

(Scale from 0 to 10, where 10 is best possible work capacity).The Hospital Anxiety and Depression Scale (HADS) [61].

#### Economic evaluation

Treatment costs for the workplace intervention and the rehabilitation program will be estimated applying a micro-costing approach. Productivity costs will be calculated from sickness absence data (days) and age and gender specific wage costs from Statistics Norway. Direct costs in terms of participants’ use of health services is recorded by a questionnaire developed and used in a previous study [11]. The questionnaire is answered before the rehabilitation program and 4, 8 and 12 months after the end of the program. It consists of questions concerning the number of:days admitted to hospital departments (somatic and psychiatric) or rehabilitation centerstimes receiving medical care (e.g. general practitioner, physiotherapist, chiropractor and occupational care) or alternative treatment (e.g. homeopathy)weeks and hours per week of therapeutic work trainingcontact-points with the case worker at the The Norwegian Labour and Welfare Service

#### Qualitative studies

Data will be collected through individual interviews with participants, rehabilitations therapists and employers, and through participant observation of the rehabilitation programs and non-participant observation of the workplace intervention. All interviews will be semi-structured and based on an interview guide. Interviews will be audio-recorded and transcribed. Data from observation will be collected through written field notes.

Study A: Therapists will be interviewed individually to investigate how they attend to the return to work process within a rehabilitation program based on ACT. Interviews will take part when the therapists have gained some experience with the program and the intervention. The main topics in the interviews will be what the therapists perceive as the main aim and potential outcomes of the program, and how they attend to the participants’ return to work process during their work. Participant observation of the rehabilitation program will be conducted and will be added to the interviews as data material.

Study B: Approximately 10–15 of the workplace interventions will be followed with non-participant observation. Stakeholders taking part in the workplace intervention (participants, employers and rehabilitation therapists) will be interviewed after the workplace meeting to investigate their experiences. The main topics in the interviews will be the usability and potential outcomes of the current intervention, and how the intervention might be improved. We will aim to include triads with participants, employers and rehabilitation therapists who have attended the same workplace meeting.

Study C: Participants will be interviewed to explore their perceptions of the return to work process four months after the end of the rehabilitation program. Interview topics will be the participants’ experiences of their current work participation and expectations towards the return to work process. Data from interviews will be combined with findings from quantitative data on job satisfaction, return to work self-efficacy, and readiness, expectations, beliefs and motivation for return to work.

### Data analyses

#### Effect evaluation

Effect analyses of primary and secondary outcomes will be performed by intention to treat and per protocol. For the primary outcomes, sustainable return to work will be evaluated with survival analysis and difference in days of sick leave will be evaluated with the Mann Whitney U-test, as sick leave days are not likely to be normally distributed. Effect differences for secondary outcomes will be analysed with linear mixed models or non-parametric methods, as appropriate. Subgroup analyses will be performed for main diagnosis groups.

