### Participants and recruitment

People living in Trøndelag (two counties in Central Norway) are eligible for inclusion if they 1) are aged 18 to 60 years, 2) are sick-listed 2–12 months, 3) hold at least a 20% job position (e.g. minimum one day per week), 4) have an employer, 5) have a sick-leave status of at least 50% off work, 6) anticipate at least four more weeks of sick-leave, and 7) have a diagnosis within the musculoskeletal, psychological or general and unspecified chapters of ICPC-2. The participants’ diagnoses are as assessed by the participants’ general practitioner (GP). In addition, potential participants must currently have an employer. Exclusion criteria are: Being self-employed, having or being under consideration for a serious somatic or mental health/substance abuse disorder (assessed by the screening clinic), currently undergoing rehabilitation, having significant problems with working in a group (assessed by the screening clinic based on questionnaires and clinical interview), insufficient comprehension of Norwegian language to participate in group sessions and to fill out questionnaires, scheduled for surgery within the next 6 months, or being pregnant.

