#### Economic evaluation

We will take the societal perspective and both a cost-effectiveness, cost-utility and cost benefit approach will be applied, and in accordance with the Norwegian guidelines for economic evaluation [62]. In the cost-effectiveness analysis, sickness absence days will be used as outcome measure, and to avoid double counting productivity costs will be excluded. In the cost-utility analysis, the outcome measure is Quality Adjusted Life Years [63] based on the 15D instrument [56], and cost-utility estimates will be provided both with and without the inclusion of productivity costs. The cost-benefit analysis will compare costs and benefits taking increased treatment costs and potential societal savings from reduced sickness absenteeism into account. Analyses of cost-effectiveness and cost-utility will be performed by calculating the ratio of incremental costs divided by incremental effect. Univariate sensitivity analyses and bootstrapping procedures will be applied to estimate uncertainty surrounding the incremental ratios.

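### A primary outcome counted in days is tied to an unadjusted rank test that gives no difference in days, while the economic evaluation needs that difference on the same variable

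*Protocol article*

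**What the plan says.** All references are to the protocol article.

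- **Outcome.** Data collection, Effect evaluation, lists as a primary outcome "Total number of sickness absence days during 12 months of follow-up from inclusion, obtained by national registers". The matching research question under Effect and economic evaluation asks about "reducing sickness absence (total number of sickness absence days during 12 months of follow-up from inclusion".
- **Analysis.** Data analyses, Effect evaluation: "difference in days of sick leave will be evaluated with the Mann Whitney U-test, as sick leave days are not likely to be normally distributed". This is the only analysis named for the days outcome. No effect measure, interval or covariate goes with it, and diagnosis enters only through subgroup analyses.
- **Economic use of the same variable.** Data analyses, Economic evaluation: "In the cost-effectiveness analysis, sickness absence days will be used as outcome measure". The estimate comes from "calculating the ratio of incremental costs divided by incremental effect", and "Univariate sensitivity analyses and bootstrapping procedures will be applied to estimate uncertainty surrounding the incremental ratios".
- **Baseline spread.** Under Participants and recruitment, entrants "are sick-listed 2–12 months", have a sick-leave grade of 50% or more, and fall in one of three ICPC-2 diagnosis areas. The Randomization section describes "Block randomization with unknown block sizes" and mentions no stratification factor.

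**The concern.** The research question is about a quantity, the number of absence days, and the analysis attached to it does not estimate that quantity. Mann-Whitney asks whether a person in one arm tends to rank below a person in the other. A significant result would not say how many days were saved.

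The reason given for the choice is non-normality. Days over one year are bounded, the sample-size section expects no loss to follow-up for register outcomes, and at least 80 people per arm are planned. Under those conditions a difference in means with a bootstrap or robust interval is workable. The economic section already takes that route for the same variable: a ratio of incremental cost to incremental effect needs a difference in days as its denominator, and bootstrapping the ratio resamples that difference.

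At stake is the coherence of the two headline results. The clinical result would rest on ranks and the cost-effectiveness result on what is, in effect, a mean difference. If the intervention brings most people back sooner but leaves more people absent for most of the year, ranks can favour it while total days do not. A plain Mann-Whitney test also leaves unused the prior sick-leave length, grade and diagnosis that are already recorded at entry.

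**Working it through.** **1. The plan's own figure.** The only sample-size figure is 63 per group for the log-rank test (hazard ratio 0.6, alpha 0.05, beta 0.20). Freedman's formula, two-sided: events = (1.960 + 0.842)² × (1 + 0.6)² / (1 − 0.6)² = 7.85 × 16 ≈ 126, or 63 per group if everyone has the event. It reproduces, but it concerns time to return. No figure addresses the days outcome.

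**2. Can ranks and means point in opposite directions?** A constructed example shows that they can. All values are assumed.

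- Arm A: 70% uniform on 120–240 days, 30% uniform on 240–300 days.
- Arm B: 62% uniform on 80–180 days, 38% absent for all 365 days.
- Mean A = 0.70 × 180 + 0.30 × 270 = 207.0.
- Mean B = 0.62 × 130 + 0.38 × 365 = 219.3, which is 12.3 days worse.
- Among the shorter spells, P(B > A) = (60² / 2) / (100 × 120) = 0.15, so P(B < A) = 0.85.
- Overall P(B < A) = 0.62 × (0.70 × 0.85 + 0.30 × 1) = 0.555, so ranks favour B.

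This is a proof of possibility. Nothing in the article suggests that pattern.

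**3. How often, under milder assumptions?** Simulation at 80 per arm, 3,000 trials per row. Long spells are uniform on 300–365 days (mean 332.5). Shorter spells are normal with SD 40, limited to 0–365. Mean days = p × 332.5 + (1 − p) × m, where p is the share of long spells and m the mean shorter spell. Power is at the two-sided 5% level, and the mean comparison is Welch's test.

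| Assumed pattern | Control p, m | Intervention p, m | Mean days, control / intervention | P(intervention < control) | Signs differ | Rejects: Mann-Whitney / Welch |
|---|---|---|---|---|---|---|
| No effect | 0.25, 150 | 0.25, 150 | 195.6 / 195.6 | 0.50 | 11% | 4% / 4% |
| Earlier return, more long spells | 0.20, 150 | 0.30, 125 | 186.5 / 187.3 | 0.54 | 37% | 17% / 5% |
| Stronger crossing | 0.20, 150 | 0.35, 120 | 186.5 / 194.4 | 0.53 | 44% | 11% / 8% |
| Fewer long spells only | 0.35, 140 | 0.20, 140 | 207.4 / 178.5 | 0.58 | 3% | 38% / 52% |
| Shift in shorter spells | 0.25, 150 | 0.25, 125 | 195.6 / 176.9 | 0.60 | 9% | 54% / 25% |

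The signs differ in 11% of trials by chance alone when there is no effect; crossing raises this to 37–44%. A significant Mann-Whitney result with an observed mean difference in the opposite direction occurred in about 0% of trials in every row. In the extreme example of step 2 it occurred in roughly 7%.

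**4. What adjustment is worth.** For a comparison of means, adjusting for variables that explain a share R² of the variance multiplies the effective sample by 1 / (1 − R²). The article gives no R², so 5–20% is assumed.

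- R² = 0.05: 1 / 0.95 = 1.05, so 160 participants count as about 168.
- R² = 0.20: 1 / 0.80 = 1.25, so 160 participants count as 200.

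This gain is relative to an unadjusted mean comparison, not to the Mann-Whitney test.

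**The case against.** Mann-Whitney is a valid, prespecified choice with a stated rationale, and it is not uniformly the weaker test. In the shift pattern above it has 54% power against 25% for the mean comparison. Moving to a mean could lose power, and the article gives no distribution from which to tell. This stands, and it means the change is a trade-off.

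A condensed article may also leave an effect estimate beside the test to the analysis plan. That is fair as far as omissions go. The point here is what the article does fix: a rank test, justified by a reason that the next section does not need.

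Several stronger readings are tempting and are not supported:

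- **That the trial will yield no figure for days saved.** The economic evaluation will produce an incremental effect in days. The gap is in the primary analysis.
- **That chance baseline imbalance biases the result.** Under randomisation the unadjusted test keeps its error rate; lack of adjustment costs precision. Silence on stratification in a condensed article does not show that there is none.
- **That established predictors are being ignored.** The article names none. Prior leave, grade and diagnosis are plausible candidates drawn from the eligibility rules.
- **That the return-to-work outcome has the same fault.** The article says only that survival analysis will be used, which leaves covariates open.
- **That two significant results in opposite directions are likely.** The milder simulations do not show it.

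**Conclusion.** The point holds in limited form. A primary outcome expressed in total days is attached to an unadjusted rank test that gives no difference in days, on a ground that does not rule out comparing means at 80 per arm. The economic evaluation needs a difference in days on the same variable and bootstraps the ratio built on it. That this is a difference in means is my reading of the incremental ratio; the article does not use the word.

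The two analyses can disagree in sign or significance when effects on shorter and longer spells run in opposite directions. The frequencies above rest wholly on assumed distributions. The value of adjustment, about 5–25% more participants, rests on an assumed 5–20% of variance explained. The gain is an interpretable estimate and better precision; no bias is being removed. This should be settled before analysis, but it does not invalidate the trial.

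**What to change.** Prespecify for the days outcome:

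1. The between-arm difference in mean sickness absence days over 12 months, with a bootstrap or robust 95% confidence interval.
2. Adjustment for prior sick-leave length, baseline sick-leave grade and diagnosis chapter, described as plausible prognostic variables.
3. The Mann-Whitney test reported beside it, with one of the two named in advance as the deciding analysis. The mean difference matches the research question and the economic ratio; the rank test may have more power if the effect is a shift among shorter spells. The choice should be made openly on those grounds.
4. The same adjusted estimate as the incremental effect in the cost-effectiveness ratio.

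The cost is analysis-plan wording, fixed before anyone sees results by arm. No new data are needed, because all three variables are known at inclusion from eligibility and register information. The price is the possible loss of power named in item 3.
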